### 1.5. Trial Design

To explore feasibility and ensure adequate implementation modalities, a pilot study was conducted in March/April 2022.

Subsequently, we plan to conduct a multi-site, non-blinded, 1:1 cluster-randomised controlled trial (cRCT) with two arms used to assess efficacy: the (1) intervention group (receiving the Family United programme) and (2) waitlist/control group (families only receiving the Family UNited programme after the completion of all data collection points).

We will prospectively collect all outcome data, assessing changes in parenting skills and family adjustment in caregivers, children’s behaviour, resilience capacities, and attitudes towards peer violence.

To assess programme delivery, fidelity, feasibility, and acceptability, we aim to include an embedded process evaluation.

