### 2.7. Sample Size

In the pilot study, 26 caregivers (17 in Parma and 9 in Trentino) completed the data collection before the intervention; whereas, only 18 caregivers (11 in Parma and 7 in Trentino) completed the data collection 2 weeks after the intervention. Overall, 19 children (11 in Parma and 8 in Trentino) completed both data collections. Based on the completion of both time points and excluding missing data, the following sample sizes were estimated. To keep the power at 80%, and to be able to show results for each of the scales, the sample size was calculated to be 40 participants in each group, resulting in a total number of families of 160, as shown in Table 4 and Figure 2.

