Regression analyses (SEM) will also be conducted between the parental dimensions and the filial dimensions to evaluate the effect of parental change on the behaviour and emotional state of the child.

Stratified analyses will be conducted by gender, as well as for participants with worse scores (below the 33rd or above the 66th percentile) at baseline. Statistical significance will be set at a *p*-value lower than 0.05.

Qualitative data will be analysed using thematic analysis (TA) [31], where dominant themes will be identified through a close examination of the data. First, open coding will be carried out and an initial coding schedule will be devised in order to define each emerging theme. The coding manual will then be revised throughout the coding of the remaining transcripts. The original codes will frequently be combined or divided into further codes, depending on the emergent findings. Themes will be continually compared with newly coded interview transcripts to ensure that they are readily applicable to the data by using the research team’s familiarity with the text and coding manual to frequently assess and reassess how the codes are being applied to the raw data. The coding manual will be discussed within the research team and amendments will be made if necessary. The team will then develop a revised code set that includes the new and combined codes. NVivo9 software will be used to facilitate the analysis. The analysis will cease when the research team judges that thematic saturation has been reached [31].

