Week 3–6	Families take part in weekly sessions of Family UNited for 4 weeks
Week 6	All families’ complete measures again (Time 2)
	RCT
Week 1–2	Research Assistants assess families for eligibility and inform them about the planned trial and the programme verbally and in writing
Week 3	Research Assistants recruit 160 families, obtain written assent/consent and conduct baseline measures (Time 1; pre-intervention) with all families After data collection has been completed, families are randomly allocated to intervention or control group
Week 4–7	Intervention group families take part in weekly sessions of Family UNited for 4 weeks Facilitators and observers complete process evaluation tools after each session
Week 9	ALL families complete measures again (Time 2; post-intervention). 10 caregivers from the intervention group are interviewed for acceptability
Week 13	ALL families complete measures again (Time 3; follow-up)
Week 14–17	Control families take part in weekly sessions of Family UNited for 4 weeks

**Table 4 ijerph-20-06548-t004:** Sample size estimates based on selected (statistically significant in paired *t*-test *) results from the pilot trial for Family UNited in Parma and Trentino, Italy, in spring 2022 [25].

	Before: Mean ± SD	After: Mean ± SD	Paired Difference in Means ± SD	Sample Size (Power)	
PAFAS				80%	90%
Positive encouragement (*n* = 14)	5.1 ± 2.3	2,1 ± 1.2	3.0 * ± 2.7	**10**	**12**
Parental adjustment (*n* = 14)	5.9 ± 3.1	4.7 ± 2.7	1.2 ± 2.7	**40**	**54**
Family relationships (*n* = 14)	3.8 ± 2.3	2.9 ± 1.7	0.9 * ± 1.2	**17**	**21**
SDQ					
Hyperactivity (*n* = 14)	2.8 ± 2.1	2.1 ± 1.8	0.7 * ± 1.1	**23**	**30**
Conduct problems (*n* = 14)	2.6 ± 1.8	1.3 ± 1.1	1.4 * ± 1.4	**12**	**15**
Total Difficulty Scale (*n* = 14)	10.9 ± 5.0	8.4 ± 4.4	2.6 * ± 3.7	**20**	**26**
CYRM-R					
Total CYRM (*n* = 12)	58.8 ± 19.0	60.8 ± 18.2	1.9 ± 6.9	**104**	**138**
Personal resilience (*n* = 12)	35.8 ± 11.8	37.4 ± 11.3	1.7 ± 3.9	**45**	**61**

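### The 80% power claimed for each scale with 160 families is not delivered: nothing is added for attrition or school randomisation, and Table 4 itself lists larger sizes for two scales

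*Protocol article*

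**What the plan says.** Section 2.7 gives the aim as "To keep the power at 80%, and to be able to show results for each of the scales" and concludes that "the sample size was calculated to be 40 participants in each group, resulting in a total number of families of 160". It describes the data behind the figure in these words: "Based on the completion of both time points and excluding missing data, the following sample sizes were estimated". It also reports that 26 caregivers gave baseline data in the pilot and that "only 18 caregivers (11 in Parma and 7 in Trentino) completed the data collection 2 weeks after the intervention".

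Table 4 sets out the estimates. Its effect column is headed "Paired Difference in Means ± SD", so each row is a within-person change in a pilot that had no control group. The 80% column lists 10, 40 and 17 for the three PAFAS rows, 23, 12 and 20 for the three SDQ rows, and 104 and 45 for the two CYRM-R rows.

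The trial is a "multi-site, non-blinded, 1:1 cluster-randomised controlled trial (cRCT) with two arms used to assess efficacy" (section 1.5). Section 2.9 says that schools are the units randomised. Section 2.11.3 describes one group-by-time mixed ANOVA with subject and territory as random effects, at this threshold: "Statistical significance will be set at a *p*-value lower than 0.05". Table 3 makes 160 the number of families recruited at baseline.

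**The concern.** A size worked out for completers in one group is used as the recruitment target of a two-arm trial randomised by school. The same paragraph reports a substantial loss between the two pilot measurements, yet the total has no margin for it. It has no margin either for similarity between families in the same school. The claim is also made for every scale, although the table it cites gives two scales a requirement above 40.

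What is at stake is how a null result would be read. If Parental adjustment or child resilience shows no difference, readers will take it as the answer of a trial with 80% power. For those scales the chance of detecting the pilot-sized effect may be nearer one half, and for Total CYRM it is well below that.

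**Working it through.** **Inputs from the article.** Table 4 means and SDs of paired change; 160 families allocated 1:1, so 80 per arm; significance level 0.05, taken as two-sided; pilot caregivers 26 falling to 18, so retention is 18/26 = 0.692.

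**Assumptions not in the article.** 12 families recruited per school, borrowed from the delivery group size in section 2.3; ICC of 0.02 or 0.05; no change in the control arm; equal SD of change in both arms.

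**Step 1: reproduce the stated 40.** The one-group paired formula is n = (1.96 + 0.842)² × (SD/difference)². For Parental adjustment (1.2 ± 2.7, standardised effect d = 0.444) it gives 7.85 × (2.7/1.2)² = 39.7, so 40. At 90% power it gives 53.2, so 54. Both match Table 4. Total CYRM (1.9 ± 6.9) gives 103.5, so 104, as stated. The exact paired t-test gives 9, 16, 22, 10, 18 and 44 for the other six rows, against the stated 10, 17, 23, 12, 20 and 45. One-sided testing would give 32 for Parental adjustment and does not fit. The column is therefore a one-group paired calculation, and 160 = 4 × 40 with no further factor.

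**Step 2: the two-arm requirement.** Comparing mean change between arms needs twice the paired number in each arm: 2 × 39.7 = 79.5 by the normal formula, or 80.4 by the t-test. With 80 per arm, power is about 80%.

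**Step 3: attrition.** 80 × 0.692 = 55.4 per arm. Two-sample t power at d = 0.444 is 64%.

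**Step 4: attrition and clustering.** Families left per school: 12 × 0.692 = 8.31. Design effect: 1 + 7.31 × ICC, which is 1.146 at ICC 0.02 and 1.365 at ICC 0.05. Effective size per arm: 55.4/1.146 = 48.3 and 55.4/1.365 = 40.6. Power is 58% and 51%.

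**Step 5: all eight scales, same method.**

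| Scale | d | 80 per arm, no loss, ICC 0 | 69% kept, ICC 0 | 69% kept, ICC 0.02 | 69% kept, ICC 0.05 |
|---|---|---|---|---|---|
| Positive encouragement | 1.111 | >99% | >99% | >99% | >99% |
| Parental adjustment | 0.444 | 80% | 64% | 58% | 51% |
| Family relationships | 0.750 | >99% | 97% | 95% | 92% |
| Hyperactivity | 0.636 | 98% | 91% | 87% | 81% |
| Conduct problems | 1.000 | >99% | >99% | >99% | 99% |
| Total Difficulty | 0.703 | 99% | 96% | 93% | 88% |
| Total CYRM | 0.275 | 41% | 30% | 27% | 23% |
| Personal resilience | 0.436 | 78% | 62% | 56% | 49% |

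The 69% is caregiver retention. The article gives no baseline count of pilot children, so applying it to the two CYRM-R rows is a further assumption. The first power column does not depend on it.

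**Step 6: sensitivity to the analysis.** The Table 4 SDs for Parental adjustment (3.1 before, 2.7 after, 2.7 for the change) imply a correlation of (3.1² + 2.7² − 2.7²)/(2 × 3.1 × 2.7) = 0.57. A baseline-adjusted comparison then has SD 2.7 × √(1 − 0.57²) = 2.21 and d = 0.54. At 69% retention power is about 81%, 75% and 68% at ICC 0, 0.02 and 0.05.

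**The case against.** The strongest reply is that 160 is adequate for the scale that set it. Two sites by two arms at 40 each gives 80 per arm, and step 2 shows that this meets the two-arm requirement. This stands. A reader might infer that the missing control arm makes 160 too small, or that power is only about 50% because 40 are compared with 40. The article does not support that: it gives 160 families throughout and describes one analysis pooled over sites. The 50% would apply only to a single site analysed alone, which is not planned.

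A reader might also say that 40 in each of two groups makes 80, not 160. The text does not explain the step, but it points to Figure 2, which is not available here, and two sites by two arms is the natural reading. That is a matter of wording.

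A harsher retention figure is also tempting, because only 14 of the 26 pilot caregivers enter the Table 4 caregiver rows. That count excludes missing data. The trial allows imputation (section 2.11.3) and drops a respondent only above 30% missing (section 2.11.2). Section 2.6 adds that delivery and recruitment were optimised after the pilot. The documents support 69% as observed caregiver retention, but not 54% as the expected yield.

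Finally, five of the eight scales keep at least 80%, and baseline adjustment would recover part of the loss for Parental adjustment. Both points are right and limit the finding. Neither rescues a claim made for every scale.

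**Conclusion.** The stated power is wrong as written, for two separate reasons.

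First, for Parental adjustment the 80% needs every recruited family to be retained and no clustering by school. The pilot's own retention alone lowers it to 64%. Clustering lowers it further, to 58% or 51% under the assumed ICC and school size. The attrition step rests only on figures in the article. The clustering step does not, and a small number of schools would reduce power more.

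Second, Table 4 contradicts the claim without any assumption about losses or clustering. Its 104 and 45 both exceed 40, and 104 exceeds even the 80 per arm. Two-arm power with full retention is about 41% for Total CYRM and 78% for Personal resilience.

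It would go too far to call the whole trial underpowered. Positive encouragement, Family relationships, Hyperactivity, Conduct problems and Total Difficulty stay at or above 80% at 69% retention and ICC up to 0.05. All these figures take the uncontrolled pilot change as the between-arm effect. Any improvement in the control arm would lower them.

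**What to change.** Keep 160 families. Rewrite section 2.7 and Table 4 as follows:

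- Base the calculation on the between-arm comparison with 80 families per arm, and say that 40 is per arm per site, if that is what is meant.
- Apply the pilot's caregiver retention (18 of 26), and state an ICC range and the expected number of families per school as assumptions.
- Replace the claim for each of the scales with power scale by scale, naming the scales for which 80% holds.
- Give the figures for the analysis actually chosen. At 69% retention and ICC 0 to 0.05, Parental adjustment has about 51–64% for change scores and about 68–81% for a baseline-adjusted comparison. The two ranges should not be mixed.

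The cost is one paragraph and one table, with no added families. The drawback is that the stated power becomes less favourable for Parental adjustment and the two CYRM-R scales.

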### 2.8. Recruitment of Families

Families in the Trento province will be invited to the project through advertising in youth gathering centres and centres for families, schools, etc. The recruitment will use both formal channels (e.g., Agency for Social Cohesion of the Autonomous Province of Trento and Schools) and informal channels (e.g., social networks, WhatsApp parent groups, etc.). In Parma, families will be recruited through schools and probably through some companies willing to advertise. The City of Parma and the local health authority will put notices on their respective sites.

### 2.9. Allocation

Once families agree to participate in this study and the first data collection has been completed, they will be allocated to either take the programme immediately (intervention group) or to come back for the next two data collections and, only then, for the programme (waitlist/control group), depending on the school they will attend the programme in. To facilitate the process and to reduce interference between the two groups, the schools will actually be randomised into intervention and control groups using online software (www.sealedenvelope.com; accessed on 28 January 2022). A cluster randomization, instead of a complete randomization, will be used, due to the peculiar logistical needs deriving from the structure of the territory. We are aware that randomization before recruiting participants can influence recruitment and dropout in the control arm. To minimise these issues, we will instruct staff not to reveal family allocation until families have agreed to take part, signed the informed consent form, and completed the baseline data collection. This is an unblinded trial. Research assistants, staff, and families will be aware of participants’ allocated conditions after the first measurements are completed and during the remaining time of the trial.

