## 2. Materials and Methods

### 2.1. Study Setting

This study will take place in different schools in Parma city and Trento province, Italy. The exact location will be decided by the Italian researchers of this study after conducting local assessments for the suitability of the location. Parma city has a population of 194,417; whereas, 538,223 persons live in the Trento province. Parma and Trento are two rich cities in the Italian national scene, located in two of the wealthiest and most-developed regions of Italy, Emilia-Romagna and Trentino-Aldo Adige, with a GDP per capita of 33.6 and 36.9 (in thousand EUR), respectively [20]. In both cities, there are problems of youth addiction due to a number of possible reasons, including the social disintegration of a large number of immigrants, including second-generation immigrants [21]. In their study, Deolmi et al. indicate that 31% of the participants with mental disorders, which includes drug use and addiction, are of immigrant origins [21]. This could be partly explained by the difficulties in integration faced by immigrants when settling down in host countries [22].

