### 2.3. Intervention Condition

Family UNited will be delivered to families in groups of approximately 12 families. Only one or two parents or main caregivers will be invited to attend, with a maximum of two children under their care aged 8 to 15 years.

The programme consists of four meetings (Table 1) spread over four weeks. In the first hour of each week, two facilitators will work with caregivers in one room; whereas, the other two facilitators will work with the children in a separate room. In the second hour of the meeting, all four facilitators and all caregivers and children will come together in one room for the joint family session.

During the caregiver sessions, caregivers will learn about children’s behaviour and how caregiver attention changes children’s behaviour. They will learn techniques to make the behaviour they want to see more likely to happen. They will practice how to communicate with their children in a way that is healthy and promotes listening. They will also be shown ways to make sure their children know that they are loved and, at the same time, how to set limits that help the children stay safe and feel secure.

During the child sessions, children will learn about some good ways to deal with stress and the importance of talking to trusted adults about their feelings. They will think about their caregiver’s responsibilities and have discussions about the positive qualities they want to develop and use as adults. In addition, children will learn and practice ways to deal with peer pressure situations, increasing the likelihood that they will stay healthy and safe.

In the family sessions, caregivers and their children will come together to practice positive and respectful communication. Together, they will play games and participate in activities that encourage positive relationships and build trust. The children will enjoy one-to-one time with their caregivers while talking about the strengths and qualities they share as families and the things they can do together to demonstrate their family values.

Based on the process evaluation, we will monitor participants’ attendance at each of the sessions and calculate the “Reach” and “Dose received”, as shown in Table 2.

During the trial period, participants will be requested not to take part in any other family skills programme, nor will any other contacts be made with the families, apart from the scheduled sessions of the Family UNited programme.

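### Schools are randomised with no restriction named by site or school level, and the outcome model has no child-age term, so chance imbalance in age (and possibly site) is neither prevented nor adjusted for

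*Protocol article*

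**What the plan says.** Section 1.5 describes a "1:1 cluster-randomised controlled trial (cRCT) with two arms used to assess efficacy". Section 2.9 gives the method: "the schools will actually be randomised into intervention and control groups using online software". A family's arm follows from the venue, "depending on the school they will attend the programme in". The section names the software and the logistical reason for clustering. It does not mention stratification, blocking or matching.

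On the units, Section 2.1 says only that "This study will take place in different schools in Parma city and Trento province, Italy", and no count of schools appears anywhere. Section 2.3 states that "Family UNited will be delivered to families in groups of approximately 12 families", and the fidelity indicator in Table 2 counts programmes with more than 4 and fewer than 15 families. Section 2.7 says "the sample size was calculated to be 40 participants in each group, resulting in a total number of families of 160" and points to Table 4 and Figure 2; the figure is not available in the text reviewed.

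Families do not come through schools alone. In Trento, Section 2.8 adds "informal channels (e.g., social networks, WhatsApp parent groups, etc" and advertising in youth and family centres. For the other site it says "In Parma, families will be recruited through schools and probably through some companies willing to advertise".

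Eligible children are 8 to 15 years old (Section 2.2), and the baseline demographics questionnaire records child age (Section 2.10). The model in Section 2.11.3 is a mixed ANOVA of time by group with random effects for subject and territory. Neither child age nor school appears in it. The planned stratified analyses are by gender and baseline score.

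**The concern.** When few clusters are randomised without restriction, one arm can easily receive more venues with older children, or more venues from one site. The article's own theory makes age relevant: Section 1.3 says that caregivers' influence is greatest with younger children and falls markedly in early adolescence, and the eligible range spans that point. The sites differ in recruitment channels. In the pilot, the second data collection was completed by 11 of 17 caregivers (65%) in Parma and 7 of 9 (78%) in Trentino, although these numbers are too small to establish a difference.

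If children of different ages, or families at different sites, change differently over the trial, an imbalance mixes that difference with the programme effect in the one allocation that is realised. Even with no such mixing, age-related variation that is left in the residual costs precision. Age is already collected, and the allocation tool is already in use, so little stands in the way of dealing with both.

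**Working it through.** **1. The plan's own figure.** The 40 in Section 2.7 matches PAFAS parental adjustment in Table 4 (paired difference 1.2, SD 2.7), assuming a two-sided 5% level:

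n = ((z₀.₉₇₅ + z₀.₈₀) × SD / d)² = ((1.960 + 0.842) × 2.7 / 1.2)² = 39.7, so 40.

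At 90% power: ((1.960 + 1.282) × 2.25)² = 53.2, so 54. Both agree with Table 4. Two arms of 40 would give 80 families; 160 = 4 × 40, which fits 2 sites × 2 arms.

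**2. How many units.** The article gives no number of schools, so delivery groups are the only guide.
- At about 12 families per group: 160 / 12 = 13.3 groups, or 80 / 12 = 6.7 per arm.
- Over 5 to 14 families per group: 160 / 14 = 11.4 to 160 / 5 = 32 groups.

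Several groups may share a school, so there may be fewer schools than groups.

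**3. Chance of imbalance.** Assume K schools of equal size, half of one kind (older children, or one site), with K/2 allocated to each arm without restriction. The number x of that kind in the intervention arm is hypergeometric:

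P(x) = C(K/2, x)² / C(K, K/2).

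| K (assumed) | Split or worse | Gap in share | Probability |
|---|---|---|---|
| 10 | 4:1 | (4 − 1)/5 = 60 points | 52/252 = 21% |
| 14 | 5:2 | (5 − 2)/7 = 43 points | 982/3432 = 29% |
| 20 | 7:3 | (7 − 3)/10 = 40 points | 33052/184756 = 18% |

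With very few schools, arm and site could coincide completely: 2/6 = 33% for 4 schools and 2/20 = 10% for 6. The site reading of all these figures applies only if allocation is not already done within site.

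**4. Does balancing site also balance age?** No. Take equal numbers of younger and older schools in each site and allocate half of each site's schools to each arm.
- K = 8: the number of older schools per site in the intervention arm is 0, 1 or 2 with probability 1/6, 4/6, 1/6. The age split is even with probability (16 + 1 + 1)/36 = 50%, so a gap of at least 50 points has probability 50%.
- K = 12: per-site weights 1, 9, 9, 1 out of 20. Even split 2 × (1 + 81)/400 = 41%, so a gap of at least 33 points has probability 59%.
- K = 16: per-site weights 1, 16, 36, 16, 1 out of 70. Even split (2 + 512 + 1296)/4900 = 37%, so a gap of at least 25 points has probability 63%.

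**5. What an imbalance does to the planned test.** Let g be the gap in the share of older children, L a stable difference in score level between age bands, and δ the difference in mean change between the bands from baseline (week 3) to follow-up (week 13), about 10 weeks.
- The level difference shifts the arm contrast by g × L at baseline and by g × L at follow-up. The time-by-group contrast is the difference of the two, so L contributes 0.
- The change difference contributes g × δ. For a 5:2 split this is 0.43 × δ. The article gives no figure for δ.
- If the response to the programme depends on age, the estimate also reflects the age mix of the intervention arm.

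The same reasoning holds for site. A random intercept for territory absorbs level differences only, and its variance would be estimated from two levels.

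**The case against.** The best reply has four parts.

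- **Site may already be balanced.** Since 160 = 4 × 40 fits 40 families per arm in each site, and Figure 2 is not available, a split within site may be intended. Territory is also in the model. This stands: the article is silent on restriction by site, which is not the same as choosing to do without it, so the site part is the weaker half.
- **Schools are venues.** Families attend the programme at a school but need not belong to it, and many are recruited elsewhere. A venue can mix ages, so the school's level is an imperfect proxy for child age. This stands too, and it makes the two-kind calculation an upper illustration for age. It does not change the fact that nothing in the article balances or adjusts for age.
- **The number of schools is a guess.** That is so; the probabilities are conditional on an assumed count, equal sizes and an exact half split.
- **An unseen analysis plan could add covariates, and the trial has begun.** Section 2.12.8 presents the article as giving access to the full protocol, and restriction of randomisation is normally fixed in the protocol. The stated model has no age term. The start of the trial (Section 4) limits the remedy for allocation but leaves the analysis open.

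A reader might go further, multiply the gap in age mix by an assumed difference in scores between age bands, and call the product a bias in the programme effect. The article does not support that: the planned test is on change from baseline, where stable differences cancel.

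**Conclusion.** The point holds in a limited form. Section 2.9 names no restriction on the randomisation of schools, and Section 2.11.3 has no child-age term. With roughly 13 delivery groups, a material chance imbalance in child age is plausible. The same is true of site if the arms are not split within site. The illustrative size is an 18% to 29% chance of a gap of 40 points or more with 10, 14 or 20 schools. That rests on an assumed number of equal-sized schools, half of each kind, allocated exactly 1:1.

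The consequence is confined to age- or site-related differences in change or in response, and to lost precision. No bias in SD units can be given, because the article has no information on how change differs by age or site. The article also does not show that the number of schools is small or that site was left unbalanced; both remain to be stated. Age is the stronger part of the point, site the weaker.

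**What to change.** - **Allocation (Section 2.9).** State the number of schools and any restriction used. Randomise schools not yet allocated 1:1 within site and, where numbers allow, within school level, for example as pairs of similar schools within a site. If allocation was already done within site, one sentence saying so settles that part.
- **Analysis (Section 2.11.3).** Fit site as a fixed effect in place of a two-level random effect, and add child age from the baseline demographics questionnaire. Include the interaction of each with time, because a main effect alone does not touch differences in change. A baseline-adjusted arm comparison with age and site as covariates would serve equally well.
- **If all schools are already randomised**, make the analysis change only, and record it before outcome data are examined. It cannot help if arm and site turn out to coincide.

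The cost is a few degrees of freedom and some wording, with no additional families or data. The main risk is crossing site and school level fully among few schools, which can leave strata with a single school and nothing to balance. Pairing, or stratifying by site alone with age handled in the model, avoids this.

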### 2.2. Eligibility Criteria

Participants will be parents or caregivers and one child under their care aged between 8 and 15 years. Sampling will be opportunistic, using a ‘universal’ approach in which facilitators will recruit families from the general population, not targeting specifically those with particular difficulties or risks. The inclusion criteria are caregivers who speak Italian and have at least one child under their care, aged 8 to 15 years, willing to take part in the programme and those in the area for the duration of the whole study. Families who took part in any other family skills training programme in the past 24 months, or where the caregiver lives separately from the child or does not have a constant relationship of attendance with the child (i.e., less than half of the time in cases of shared custody), will be excluded from this study.

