### 2.4. Waitlist/Control Condition

Participants allocated to the waitlist/control group will only receive the questionnaires at the same time as the families in the intervention group. They will not receive any family skills intervention, nor will any contact be made with facilitators before all data have been collected. Only then the waitlist/control families will start the Family UNited training programme, as shown in Figure 2.

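### Section 2.9 and Table 3 disagree on what is randomised and when, and no stated step keeps the school list from those who recruit

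*Protocol article*

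**What the plan says.** **Unit and timing.** Section 2.9 states that "the schools will actually be randomised into intervention and control groups using online software". It describes this as a draw made ahead of recruitment and names the risk: "We are aware that randomization before recruiting participants can influence recruitment and dropout in the control arm". A family's arm is settled "depending on the school they will attend the programme in". Table 3 (RCT, week 3) reads differently: "After data collection has been completed, families are randomly allocated to intervention or control group".

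**Safeguard.** Section 2.9 answers the risk it names with one measure: "we will instruct staff not to reveal family allocation until families have agreed to take part, signed the informed consent form, and completed the baseline". It closes by saying that research assistants, staff and families will know participants' "allocated conditions after the first measurements are completed and during the remaining time of the trial".

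**Who recruits, and where.** Section 2.2 says that sampling is opportunistic and that "facilitators will recruit families from the general population". Table 3 gives recruitment, consent and baseline measurement of all 160 families to research assistants. Section 2.8 lists schools as one channel among several. The others include youth and family centres, social networks, parent messaging groups, companies, and notices on city and health-authority sites.

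**Schedule.** Table 3 completes recruitment and baseline in week 3 and starts sessions in week 4.

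**The concern.** In a cluster trial, individuals recruited after the clusters have been drawn are protected from selection only if those who approach and enrol them do not know the cluster's arm. Keeping the arm from the family is a weaker protection. A recruiter who knows the list can still influence whom to approach, how hard to persuade, or which school to suggest.

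The last route is particular to this trial. A family that answers a website notice or a company advertisement has no evident link to one school, yet its arm depends on the school it will attend. The article gives no rule for assigning that school.

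At stake is the comparability of the arms in things that baseline questionnaires capture poorly, such as motivation and expectation of benefit. Outcomes are caregiver and child questionnaires, and families know their arm at both follow-ups, so such differences could pass for a programme effect.

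**Working it through.** **1. The passages side by side (protocol article).**

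| Item | Section 2.9 | Elsewhere |
|---|---|---|
| Unit randomised | School | Family (Table 3) |
| Time of the draw | Before recruitment | After week-3 baseline (Table 3) |
| When staff know | After the first measurements; but staff are told not to reveal allocation before then | Not stated |
| Rule linking a family to a school | None stated | Section 2.8 lists channels not tied to a school |
| Who recruits | "Staff", no role given | Facilitators (section 2.2); research assistants (Table 3) |

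The opening sentence of section 2.9 also places family allocation after the first data collection. If the school draw comes earlier, that sentence describes when a family enters or learns its arm, not when randomisation takes place. Table 3 makes no such distinction.

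**2. What the safeguard covers.** An instruction not to reveal an allocation has a purpose only if staff might hold it. The closing sentence of section 2.9 says that they learn it later. Nothing that would bring this about is described, such as a separate list-holder. Concealment from recruiters is therefore neither established nor excluded.

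**3. Whether a later draw affects the sample size.** The plan's figure is 40 per group at 80% power (section 2.7). It matches the parental adjustment row of Table 4: paired difference 1.2, SD 2.7. With two-sided alpha 0.05 (sidedness assumed) and n = (SD × (z₀.₉₇₅ + z_power) / difference)²:

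- 80% power: (2.7 × (1.960 + 0.842) / 1.2)² = 39.7, so 40, as stated.
- 90% power: (2.7 × (1.960 + 1.282) / 1.2)² = 53.2, so 54, as stated.

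The total of 160 equals 40 × 2 arms × 2 sites; the factor for sites is inferred. None of these inputs depends on when schools are drawn, so a later draw leaves 160 unchanged. Whether this formula suits the design is a separate matter.

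**4. What kind of imbalance would matter.** Section 2.11.3 plans a mixed ANOVA with time and group. Suppose that recruitment shifts the arm difference by b₁ at baseline and b₂ at follow-up. The time-by-group contrast then carries a bias of b₂ − b₁. If b₁ = b₂, it cancels. If families in one arm are more motivated, or one arm regresses further to its mean, b₂ − b₁ is not zero.

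**5. Illustration only, on assumptions not in the document.** Take 80 families per arm, no true effect, no clustering, and a recruitment-induced difference d, in SD units, in the quantity tested (here, the change). The standard error is √(2/80) = 0.158. The chance of p < 0.05 is 1 − Φ(1.96 − d/0.158) + Φ(−1.96 − d/0.158).

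| d (SD) | Chance of a significant result |
|---|---|
| 0 | 5% |
| 0.1 | 10% |
| 0.2 | 24% |
| 0.3 | 48% |

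A test that allowed for clustering would have a larger standard error and a smaller increase.

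**The case against.** The strongest reply is that the design is clear and only the table is loose. The abstract and section 1.5 call the trial cluster-randomised, section 2.9 gives the school as the unit, and Table 3 may be shorthand for when a family enters its arm. That is plausible, and it is why the point asks for reconciliation and does not claim that a second randomisation scheme is intended. It leaves open the timing of the draw and who can see the list.

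Several stronger readings are tempting but not supported:

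- *Recruiters know each school's arm.* A reader might infer this from the non-disclosure instruction, but the closing sentence of section 2.9 says that staff become aware later. The supported claim is that no mechanism is stated.
- *Staff steer families between schools.* The article does not say that staff choose the school. It is silent on how the school is chosen, which makes steering possible and no more.
- *Recruitment by facilitators breaks the waitlist rule.* Section 2.4 says "nor will any contact be made with facilitators before all data have been collected", but of participants already allocated to control. Recruitment comes before a family enters its arm. The real discrepancy is between section 2.2 and Table 3.
- *Randomisation is unstratified, with few schools per arm.* The article does not mention stratification and gives no number of schools. Dividing 160 families by groups of about 12 counts delivery groups, not schools.
- *The bias can be scaled against the 2.6-point change in Total Difficulties in Table 4.* That figure is a within-family change before and after the programme. A between-arm difference in level is a different quantity and would largely cancel in the planned test.

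Finally, section 4 says that the trial has started, so a later draw may no longer be open for some or all schools. That limits the remedy, not the point.

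**Conclusion.** The point holds in a limited form. The article states the unit and timing of randomisation inconsistently and names two different recruiting roles. It offers non-disclosure to families as the only answer to a recruitment risk that it raises itself. Selective recruitment or steering is possible; the document does not show that it occurs.

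No size can be derived. The illustrative 10% to 48% rests on assumed differences of 0.1 to 0.3 SD in change and on independent families. It shows only that modest differential change would matter. The point assumes that no unpublished procedure already conceals the school list. If one exists, what remains is the wording of Table 3, the school-assignment rule and the recruiting role.

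**What to change.** **For schools not yet randomised:**

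- Record each family's school at consent, by a written rule, and lock it.
- Randomise the schools after all week-3 baselines and before week 4, with the list held by someone who does not recruit.
- Correct Table 3 to say that schools are allocated, and make the timing in section 2.9 match.
- State in section 2.2 that research assistants recruit, as Table 3 has it.

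**For schools already randomised:** keep the list from recruiters, apply the same locked assignment rule, and report consent rates and baseline characteristics by arm.

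**Cost:** changes of wording, one nominated list-holder, and a later run of the same online randomisation. Sample size is unchanged. The real downside is that schools and facilitators would have only short notice to arrange rooms and staffing before week 4. The late draw works only if the school is locked first, and it does nothing about dropout once families learn that they are on the waitlist.
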